#### Recruitment

All participants will be recruited from the Department of Orthopedics, Kasturba Hospital, Manipal. An orthopedician will conduct an initial assessment of the participants with sub-acute and chronic mechanical neck pain. Subjective and objective evaluations including the physical examination will be performed by the orthopedician. In addition, cervical X-rays of the participants with the clinical features of MNP will be done to rule out serious pathology of the cervical spine. The patients with MNP without any red flag symptoms for manual therapy will be recruited. Since the orthopedician is at the first level of recruitment principal investigator will keep him updated regarding the progress of the trial every week to achieve adequate recruitment of the participants.

#### Recruitment status

Anticipated date of enrollment of first participant – July 10, 2020.

### Methods: assignment of interventions

#### Allocation

##### Sequence generation

Random assignment of participants to either control or the intervention group will be conducted at an allocation ratio of 1:1. The sequence will be computer-generated using R software, with two strata, which include group 1: age (18–30) and group 2: age (31–45). Sixteen blocks of 10 people (5 in the control group and 5 in the intervention group) will be used.

##### Allocation concealment mechanism

Neither the investigator nor the outcome assessors will involve in the enrolment or allocation process. The person who will not be involved in the trial will make the randomization schedule and pack the sequentially numbered, opaque, and sealed envelopes, which will be used to randomize the participants.

##### Implementation

The participants who fulfill the inclusion criteria and give consent for participating in the trial will be randomized. The member not involved in the trial will do randomization. Randomization numbers and the therapy group’s corresponding code will be available within the closed envelopes. Staff responsible for recruitment will not receive any information about the allocation of groups.

##### Blinding

The intent of the study, i.e., a comparison between the two different treatment regimens, will be explained to the patients, and the outcome assessor will be blinded.

##### Emergency unblinding

As the interventions can be modified based on the patient’s pain threshold and response, there is less likelihood of circumstances where unblinding will be required. If there is any adverse effect, the participants will be referred back to the orthopedician for further evaluation. The principal investigator after discussing with the orthopedician may modify or discontinue the treatment protocol based on his suggestion.

### Methods: data collection, management, and analysis

#### Data collection methods

##### Data collection

After obtaining written consent, the investigator will assess and evaluate the patients. The same outcome assessors will perform all post-allocation assessments.

##### Retention

The investigator will maintain periodic communication by sending text message reminders for all scheduled treatment as well as follow-up appointments. The investigator will also maintain consistency in implementation and flexible with the study schedule. The participants will be offered to reschedule their appointment within the allotted time interval between the sessions, in case of inability to attend their scheduled treatment session and follow-up assessment.

#### Data management

The patient will fill all the patient-reported questionnaires; the therapist/outcome assessor will fill the outcome measures in paper formats, provided separately. Consequently, all data will be entered electronically, including the Google forms data (online as well as paper-based) will be saved on a secured drive at the study setting. All the original files of the participants will also be stored in a secure and accessible place.

#### Statistical methods

For all the continuous primary and secondary outcomes listed in Table 2, where repeated measurements are to be taken, repeated measures ANOVA will be used. The Student’s *t* test will compare the intervention group (IG) and the control group (CG) during interim assessments. The difference in means will be used for the analysis of continuous variables. All statistical tests will be carried out at a 5% (two-sided) significance level. All analyses will be carried out using the R software, which is open-source software. Patients will be stratified into group 1 ages 18–30 and group 2 ages 31–45. Subgroup analysis will be done based on these groups.

**Table 2 Tab2:** Summary of reporting outcome measures

Variables/outcomes	Methods of analysis

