#### Trial design

The FaCe-Man trial is a pragmatic, outcome assessor-blinded, randomized, controlled superiority trial with two parallel groups. Randomization will be implemented as stratified (age-based) block randomization with a 1:1 allocation ratio. The trial report is based on the SPIRIT guidelines and checklist-2013 [36] (Additional file 1) and TIDieR guidelines for intervention description and replication [37, 38] (Additional files 2 and 3).

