#### Sample size

The sample size is estimated based on the primary outcome NPRS. The threshold for MCID in MNP patients with and without UE symptoms is 2.2 and 1.5, respectively [51], whereas the MCID for NPRS in patients with chronic musculoskeletal pain is 1 [52]. Thus, MCID is considered as one in order to have a substantial sample size in this trial.
$$ n=\kern0.5em \frac{2\ \left({Z}_{1-\alpha /2}+{Z}_{1-\beta}\right).\kern0.5em {\sigma}^2\left[\ 1+\left(m-1\right)\rho \right]}{m{d}^2} $$

*d* - MCID = 1

Z_1-α/2_ = 1.96 at *α*=0.05

Z1-β = 1.28 at 90% power

*m* = Number of time points/follow-ups = 5

*ρ* = Intraclass correlation = 0.4

$$ n=\frac{2\times {\left(1.96+1.28\right)}^2\times 2.{5}^2\times 2.2}{5\times {1}^2}=\mathbf{58} $$

Accounting for dropout rate/non-response rate

*N*^*x*^ = *N*/1 – dropout rate; for 10% dropout rate

Required sample size = **64** participants/group.

Total number of participants in the trial = **128**

To detect a difference of one on the NPRS scale (pain intensity) between the groups assuming a standard deviation of 2.5 at a 5% level of significance and 90% power and 10% dropout, the minimum number of participants required in each group is **64**.

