#### Statistical methods—analysis population and missing data

Regardless of the protocol adherence, all key analyses will be conducted as intention-to-treat (ITT) analyses, including all randomized participants. If there is any missing outcome datum, multiple imputation methods will be done, so that a complete dataset will be available for the ITT analysis.

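### The primary NPRS analysis is a repeated measures ANOVA on change that adjusts for neither baseline pain nor the randomisation stratum, so it gives up precision that the trial could have without extra patients

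*Protocol article*

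**What the plan says.** Under Statistical methods, the protocol article fixes one model for every continuous outcome with repeated measurements: "where repeated measurements are to be taken, repeated measures ANOVA will be used". Table 2 assigns it to the primary outcome, NPRS, over baseline, 3 months and 6 months. The section on the numeric pain rating scale says the result will be the between-group difference in mean change, and Table 4 is laid out for differences in change. No covariate is named.

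The Trial design section states: "Randomization will be implemented as stratified (age-based) block randomization with a 1:1 allocation ratio". The strata are ages 18–30 and 31–45 (Sequence generation). Statistical methods mentions them again, but only to add: "Subgroup analysis will be done based on these groups".

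The analysis set is all randomised participants. For missing outcomes, "multiple imputation methods will be done, so that a complete dataset will be available for the ITT analysis".

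**The concern.** Baseline NPRS enters the planned analysis as part of the response, either as a level of time or subtracted in a change score. In both cases the between-group contrast is a difference in change, which takes the full baseline value off the follow-up value. When baseline and follow-up are only moderately correlated, this adds baseline noise to the estimate. Using baseline as a covariate takes off only the part that predicts follow-up, and is at least as precise at any correlation.

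At stake is power for the primary comparison. The trial is planned with "Z1-β = 1.28 at 90% power", but the sample size formula is for a mean of follow-up scores with no baseline term, so it does not describe the planned change analysis. Leaving the stratification factor out of the model usually makes standard errors somewhat too large, which is a further, smaller loss.

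**Working it through.** **Inputs.** From Sample size: "To detect a difference of one on the NPRS scale (pain intensity) between the groups assuming a standard deviation of 2.5"; within-patient correlation ρ = 0.4; "Number of time points/follow-ups = 5"; 10% dropout. From Statistical methods: "All statistical tests will be carried out at a 5% (two-sided) significance level". The number of completers is contested within the article. The abstract's 160 less 10% gives 72 per group; the sample size section calculates 58 per group before dropout. Both are used below.

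**Assumptions.** SD 2.5 at every visit including baseline, equal correlation between all visits, and a 1-point effect at every follow-up visit that is averaged.

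**The plan's own figure.** 2 × 3.24² × 6.25 × 2.2 / 5 = 57.7, so 58. The factor 2.2 does not follow from the stated inputs: 1 + (5 − 1) × 0.4 = 2.6, which gives 68.2, so 69. That is a separate point. What matters here is that neither version contains a baseline term.

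**Variance factors** (multiples of SD² per patient, mean of m follow-ups):
- Follow-up only: P = [1 + (m − 1)ρ] / m
- Change from baseline: P + 1 − 2ρ
- Baseline-adjusted: P − ρ²

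For m = 2 (3 and 6 months) and ρ = 0.4, P = 1.4/2 = 0.70:
- Change: 0.70 + 1 − 0.80 = 0.90
- Adjusted: 0.70 − 0.16 = 0.54
- Variance saving: 1 − 0.54/0.90 = 40%

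The change contrast (0.90) is even less precise than ignoring baseline (0.70), as happens whenever ρ is below 0.5.

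**Standard errors and power.** SE = √(2 × 6.25 × factor / n). With 72 per group, SE is √(12.5 × 0.90/72) = 0.395 for change and √(12.5 × 0.54/72) = 0.306 adjusted. Power is Φ(1/SE − 1.96); where a range is shown, the lower value uses the t distribution.

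| Follow-ups averaged | Completers per group | Change | Baseline-adjusted |
|---|---|---|---|
| 2 (3 and 6 months) | 72 | 71–72% | 90% |
| 2 (3 and 6 months) | 58 | 61–62% | 83% |
| 5 (all) | 72 | 80–81% | 98% |

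The m = 5 row uses P = 2.6/5 = 0.52, so factors 0.72 and 0.36.

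**Patients needed for 90% power**, m = 2, before dropout: 2 × 3.24² × 6.25 × 0.90 = 118.1, so 119 per group for change; with 0.54, 70.9, so 71 per group adjusted. Put the other way, 72 patients per group analysed with adjustment are worth 72/0.6 = 120 per group on change scores.

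**Sensitivity to ρ**, m = 2:

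| ρ | Change | Adjusted | Variance saving |
|---|---|---|---|
| 0.3 | 1.05 | 0.56 | 47% |
| 0.4 | 0.90 | 0.54 | 40% |
| 0.5 | 0.75 | 0.50 | 33% |
| 0.7 | 0.45 | 0.36 | 20% |

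**Age stratum.** The document gives no figure from which a gain can be derived. If one assumes that the stratum explains 0 to 10% of the residual variance, the adjusted requirement moves from 71 to 64 per group (70.9 × 0.9 = 63.8).

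**The case against.** The strongest reply is that repeated measures ANOVA is a valid method, that randomisation keeps the change contrast unbiased, and that covariates are often settled in an analysis plan that is not shown here. The first two parts stand: this is a loss of efficiency and not an error of validity. The third carries less weight, because the article does not leave the model open. It names the model, puts baseline in the response and gives the strata a subgroup role only.

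It is also fair that the size depends on inputs the article does not settle: completers per group, the follow-ups averaged and ρ. The gain shrinks as ρ rises, but it is present throughout the range examined.

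Four stronger readings are tempting and should not be made.
- A reader might infer that the treatment effect is diluted by averaging over a baseline where the arms are alike. That would be so for a group main effect over all three occasions, but the numeric pain rating scale section and Table 4 plan a difference in change.
- A reader might infer that missing data will be filled in once. The missing-data section says multiple imputation; a complete dataset for analysis does not mean a single one.
- A reader might attack sphericity because visits are unequally spaced. The primary series of baseline, 3 and 6 months is evenly spaced, and spacing alone would not show a violation.
- A reader might expect separate significance tests in each age group, with a high chance that only one is positive. The article promises a subgroup analysis without saying how it is tested, and an interaction test is compatible with that wording.

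**Conclusion.** The point holds as an efficiency recommendation. The stated primary analysis adjusts for neither baseline NPRS nor the age stratum. On the protocol's inputs, adjusting for baseline reduces the variance of the 3- and 6-month contrast by 40%, and it brings power with 72 completers per group from about 71% to the planned 90%. With 58 completers, adjustment still reaches only 83%, so it does not by itself rescue the smaller sample size. These figures rest on equal SDs, equal correlation between visits and a constant 1-point effect. The direction of the gain holds across ρ from 0.3 to 0.7, and its size ranges from 47% to 20%. All of the quantified gain comes from baseline. The stratum belongs in the model because it was used to randomise, but its contribution is unknown and may be small. Nothing here implies bias or an inflated type I error.

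**What to change.** In Statistical methods and Table 2, replace the repeated measures ANOVA for NPRS with a linear mixed model on post-baseline scores. Include treatment, visit, treatment × visit, baseline NPRS (with its interaction with visit) and age stratum. Name the primary result in advance: the between-group contrast at the 3- and 6-month visits, or their mean. Use the same model for the secondary outcomes, each with its own baseline; where there is one follow-up it reduces to analysis of covariance.

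Keep all randomised patients, as the article states. The mixed model uses every observed follow-up score, and the multiple imputation already planned serves patients with none. Report the age subgroups through one treatment × stratum interaction, with stratum-specific estimates and confidence intervals.

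The cost is a change of wording. Baseline NPRS and age are collected for every patient, no visit or measurement is added, and R, the software named in the article, fits the model.

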***Primary outcome measure***	
NPRS (change of pain score during last week) [***∆t***_***0***_ ***→ t***_***3m***_***→ t***_***6m***_ ]	Repeated measures ANOVA
***Secondary outcome measures***	
PSFS (change of functions score) [***∆t***_***0***_ ***- t***_***4***_ ], [***∆t***_***0***_ ***→ t***_***3m***_***→ t***_***6m***_ ]	Repeated measures ANOVA
FABQ [***∆t***_***0***_ ***→ t***_***3m***_ ***→ t***_***6m***_ ]	
EEROM [***∆t***_***0***_ ***→ t***_***3m***_ ]	
Myofascial stiffness [***∆t***_***0***_ ***→ t***_***3m***_ ]	
Oculomotor control [***∆t***_***0***_ ***→ t***_***3m***_ ]	

*NPRS* numerical pain rating scale, *PSFS* patient-specific functional scale, *FABQ* fear-avoidance behavior questionnaire, *EEROM* elbow extension range of motion

***t***_***0***_ baseline, ***t***_***1***_ week 1, ***t***_***2***_ week 2, ***t***_***3***_ week 3, ***t***_***4***_ week 4, ***t***_***3m***_ 3 months following the 1st treatment session, ***t***_***6m***_ 6 months following the 1st treatment session

The mean scores and corresponding 95% CIs will be reported for all the outcomes to be measured between different time points (∆t_0_ → t_6m_) as shown in Table 3. The difference in all outcomes between the interventional and control groups will be reported as shown in Table 4.

**Table 3 Tab3:** Outcomes (mean, SD)

Outcomes	Baseline/before 1st TS		Before 2nd TS		Before 3rd TS		Before 4th TS		3rd month follow-up		6th month follow-up	
	IG	CG	IG	CG	IG	CG	IG	CG	IG	CG	IG	CG
NPRS	X	X	X	X	X	X	X	X	X	X	X	X
EEROM	X	X	X	X	X	X	X	X	X	X		
PSFS	X	X					X	X	X	X	X	X
Oculomotor functions	X	X					X	X	X	X		
Myofascial stiffness	X	X					X	X	X	X		
FABQ	X	X							X	X	X	X

*TS* treatment session, *IG* intervention group, *CG* control group, *NPRS* numerical pain rating scale, *PSFS* patient-specific functional scale, *FABQ* fear avoidance behavior questionnaire, *EEROM* elbow extension range of motion

**Table 4 Tab4:** Between-group difference in change of scores

Outcome	Change in scores between the treatment sessions and follow-up														
	***∆t***_***0***_***- t***_***2***_			***∆t***_***2***_***– t***_***3***_			***∆t***_***3***_***- t***_***4***_			***∆t***_***4***_***– t***_***3m***_			***∆t***_***3m***_***– t***_***6m***_		
	IG	CG	Diff (IG & CG)	IG	CG	Diff (IG & CG)	IG	CG	Diff (IG & CG)	IG	CG	Diff (IG & CG)	IG	CG	Diff (IG & CG)
NPRS EEROM															
Outcome measures	Change in scores between treatment sessions and follow-up.														
	***∆t***_***0***_***– t***_***4***_						***∆t***_***0***_***– t***_***3m***_***– t***_***6m***_								
	IG			CG		Diff (IG & CG)	IG			CG			Diff (IG & CG)		
PSFS FABQ															
Outcome measures	Change in scores between treatment sessions and follow - up.														
	***∆t***_***0***_***– t***_***4***_						***∆t***_***4***_***– t***_***3m***_								
	IG			CG		Diff (IG & CG)	IG			CG			Diff (IG & CG)		
Oculomotor control Myofascial stiffness															

*Diff* difference, *IG* intervention group, *CG* control group, *NPRS* numerical pain rating scale, *PSFS* patient-specific functional scale, *FABQ* fear-avoidance behavior questionnaire, *EEROM* elbow extension range of motion

***t***_***0***_ baseline, ***t***_***1***_ week 1, ***t***_***2***_ week 2, ***t***_***3***_ week 3, ***t***_***4***_ week 4, ***t***_***3m***_ 3 months following the 1st treatment session, ***t***_***6m***_ 6 months following the 1st treatment session

#### Statistical methods—analysis population and missing data

Regardless of the protocol adherence, all key analyses will be conducted as intention-to-treat (ITT) analyses, including all randomized participants. If there is any missing outcome datum, multiple imputation methods will be done, so that a complete dataset will be available for the ITT analysis.

### Methods: monitoring

#### Data monitoring

##### Data monitoring committee

No separate Data Monitoring Committee (DMC) will be formed, as the Institutional Research Committee members will perform the roles of DMC. No formal stopping guidelines and corresponding interim analysis are planned.

##### Harms

The primary investigator will record the treatment-related adverse events, including any abnormal signs and acute exacerbations of symptoms during the assessment or treatment sessions. In case of the requirement of medical evaluation, the participants will be referred to the respective medical department.

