**Methods:**

This FaCe-Man trial will recruit 160 patients with subacute and chronic mechanical neck pain diagnosed using predefined criteria. Participants will be randomized to either the intervention group or the usual care group, using a random allocation ratio of 1:1. Patients in the intervention group will receive FM (4 sessions in 4 weeks) and SYP (12 weeks) whereas the standard care group will receive cervical mobilization/ thoracic manipulation (4 sessions in 4 weeks) and therapeutic exercises (12 weeks). The primary outcome is the change in the numeric pain rating scale (NPRS). The secondary outcomes include changes in the patient-specific functional scale and oculomotor control, myofascial stiffness, fear-avoidance behavior questionnaire, and elbow extension range of motion during neurodynamics test 1.

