### Interventions

In this study, usual care includes therapeutic exercises, cervical mobilization (CM), and thoracic manipulation (TM). Joint mobilization/manipulation will be provided during day 1 and the next three treatment sessions with a 1-week interval between the sessions. Patients in the intervention group will receive FM and instructions regarding home-based SYP. Instructions regarding the home-based therapeutic exercises for the usual care group and sequential yoga poses for the interventional group will be provided during the first treatment session. Regular monitoring of the exercises and SYP will be done during different treatment and follow-up sessions.

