#### Intervention adherence

Steadfast adherence to exercise-based interventions enhances the effectiveness of the interventions in rehabilitation. Studies have shown that robust exercise adherence may improve neck and back pain patients [49, 50]. The patients will be explained the significance of adhering to study guidelines of home-based rehabilitation exercises and the importance of proper form and exercise execution. The patients will also be advised to contact the investigator on events of any acute flare-up of symptoms.

Reminders via e-mail at regular intervals and Google forms will be sent. Participants will give feedback regarding the intensity, frequency, and duration of their exercise training and the difficulties in performing exercises, improving the adherence and ensuring their participation in the study. These data will be collected once in 2 weeks during the unsupervised exercises following four treatment sessions until the end of 3 months. The investigator will provide leaflets (Additional files 4 and 5) depicting the entire exercise regimen and daily logbook, which will act as reminders if the participants do not have access to the e-mails.

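### Harms recording is limited to treatment-related events, by an investigator not stated to be blinded, and no adverse-event question is scheduled for the 8 to 10 weeks of unsupervised home exercise

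*Protocol article*

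**What the plan says.** The Harms section of the protocol article contains the only rule for recording adverse events: "The primary investigator will record the treatment-related adverse events, including any abnormal signs and acute exacerbations of symptoms during the assessment or treatment sessions". The Blinding section says that the outcome assessor is blinded. It does not say so of the investigator.

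Other sections give partial cover between sessions:

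- Intervention adherence, on contact started by the patient: "The patients will also be advised to contact the investigator on events of any acute flare-up of symptoms".
- Intervention adherence, on the content of the feedback form: "Participants will give feedback regarding the intensity, frequency, and duration of their exercise training and the difficulties in performing exercises". On its timing: "These data will be collected once in 2 weeks during the unsupervised exercises following four treatment sessions until the end of 3 months". Participants also receive a daily logbook.
- Interventions, on review of the home programme: "Regular monitoring of the exercises and SYP will be done during different treatment and follow-up sessions".
- Emergency unblinding, on referral: "If there is any adverse effect, the participants will be referred back to the orthopedician for further evaluation".

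None of these four is stated to supply the harms record.

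**The concern.** The rule has three features that work against a usable harms record.

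1. Relatedness acts as a filter before recording, when it should be a classification made afterwards. An event left out because it was thought unrelated cannot be re-examined. In neck pain, an exacerbation may be a treatment effect or the natural course, so the call is often uncertain.
2. The person keeping the record is not stated to be blinded. If attribution leans differently for a novel package than for a familiar one, recorded counts can differ between arms even when the true risks are equal.
3. The rule names no occasion other than the sessions, yet a large part of the exposure is exercise at home.

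At stake is how far any by-arm table of harms can be trusted, both in the trial report and by the Institutional Research Committee, which takes the data monitoring role. The primary pain analysis is not affected.

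**Working it through.** The protocol states no event rate, safety threshold or safety sample size, so there is no figure of its own to reproduce. The check is of the schedule and the text.

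**Step 1: length of the unsupervised phase.** Inputs:

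- Fourth session. The Interventions section says "Joint mobilization/manipulation will be provided during day 1 and the next three treatment sessions with a 1-week interval between the sessions", so the fourth session falls at 0 + 3 × 1 = week 3. The key to Table 2 labels t4 as week 4. Both are used.
- End of the home programme. The Abstract gives 12 weeks and the Objectives give 3 months. Three months is 12 or about 13 weeks. Both are used.
- Frequency of home exercise: 5 days per week (Objectives).
- Feedback form: every 2 weeks in this phase (Intervention adherence).

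Unsupervised weeks = end of programme − week of fourth session; share = unsupervised weeks ÷ end of programme.

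| Fourth session | End | Weeks | Share |
|---|---|---|---|
| week 4 | week 12 | 8 | 8/12 = 67% |
| week 4 | week 13 | 9 | 9/13 = 69% |
| week 3 | week 12 | 9 | 9/12 = 75% |
| week 3 | week 13 | 10 | 10/13 = 77% |

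This is about 8 × 5 = 40 to 10 × 5 = 50 planned home sessions, covered by 8/2 = 4 to 10/2 = 5 two-weekly forms.

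**Step 2: does any stated route solicit adverse events in that window?**

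| Route | Scheduled? | Asks about adverse events? | Stated to feed the harms record? |
|---|---|---|---|
| Flare-up contact | No, started by the patient | Flare-ups only | No |
| Two-weekly form | Yes, to month 3 | No such item stated; asks about training and difficulties | No |
| Exercise monitoring | At sessions and follow-up | Not stated | No |
| Referral to the orthopedician | No, on occurrence | A referral rule | No |

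The window is not without contact, but no scheduled question about adverse events is stated for it.

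**Step 3: what each mechanism could do, under assumed values.** The documents give none of these inputs, so the results are illustrations and not estimates.

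- Under-capture. Let q be the share of events arising away from sessions and c the share of those that is captured. Share recorded = 1 − q + q × c. With c = 0, q = 0.3 gives 0.70 and q = 0.8 gives 0.20. With c = 0.5, the same values of q give 0.85 and 0.60.
- Attribution. With equal true risk, apparent risk ratio = a(intervention) ÷ a(control), where a is the share of events called treatment-related. 0.70/0.50 = 1.40; 0.50/0.70 = 0.71; 0.60/0.60 = 1.00.

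Under-capture that is equal in both arms lowers both counts but leaves their ratio unchanged. Attribution distorts the comparison only if it differs by arm.

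**The case against.** The other side has real force on several points.

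- A reader might infer that events at home are missed. The text does not support that: patients are asked to report flare-ups, complete two-weekly forms and keep a logbook. What can be said is that adverse events are not systematically asked about and that these routes are not tied to the harms record.
- A reader might take the whole 12-week home programme as unsupervised. The Intervention adherence section places that phase after the four treatment sessions.
- A reader might infer that recording happens only at sessions. The session phrase follows the word that introduces examples and may qualify only the signs and exacerbations. It is nevertheless the only timing given.
- A reader might infer that the investigator judges relatedness. The rule says who records, not who attributes.
- A reader might infer that the arms cannot be fairly compared on safety. The same rule and contact routes apply to both arms, and differential attribution is a possibility that the documents do not quantify. No safety comparison is among the stated objectives.
- Worsening pain, the most foreseeable harm, is also measured in both arms by the pain scale at six time points, and medication use is recorded. Both help, but neither replaces an adverse-event record.
- An article condenses a fuller protocol, and the actual forms are not shown. That would answer a complaint about silence. It does not answer the restriction to treatment-related events, which the article states outright.

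The last point is why the concern survives in a limited form.

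**Conclusion.** The concern holds in limited form. The stated rule discards events not attributed to treatment before that attribution can be reviewed, and it leaves the record to someone not stated to be blinded. For about 8 to 10 weeks, 67% to 77% of the period to month 3, no scheduled question about adverse events is stated. Any by-arm harms summary is therefore open to attribution bias and under-capture. Neither can be sized from the documents, and under-capture need not differ by arm.

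This rests on two assumptions: that the Harms section is the operative recording rule, and that the two-weekly form has no adverse-event item beyond what the article describes. It is a cheap improvement to harms reporting, not a threat to the primary result.

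**What to change.** Change the Harms section so that:

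1. all adverse events are recorded in both arms, regardless of attribution;
2. the same fixed question is asked in both arms at every treatment and follow-up visit, and as one item on the existing two-weekly form;
3. flare-ups that patients report between visits are entered in the same record;
4. relatedness is entered afterwards, as a separate field.

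The referral arrangements need no change. The cost is one question on forms and visit sheets already in use, with no new visits or staff. The downside is more minor events to log.
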